### Statistical analysis

#### Clinical effectiveness

Descriptive statistics will be used to describe baseline data and outcomes. Normal Q-Q Plots and the Shapiro-Wilk test will be performed to test for normality. In normally distributed continuous variables, means and standard deviations will be used. Non-normally distributed variables and ordinal variables will be expressed by medians and interquartile ranges. Categorical variables will be described by counts and percentages. Missing data will be handled by multiple imputations. Two-sided 95% confidence intervals (CI) will express the statistical uncertainty; a two-sided *p*-value < 0.05 will be considered statistically significant. Multiple testing will not be corrected for. An intention-to-treat principle will be applied to the statistical analyses.

We will perform the main analysis of the primary outcome on the change (delta) USER-Participation-R scores between 6 weeks and 12 months and a sensitivity analysis on the observed USER-Participation-R scores at 12 months. We will use a linear mixed effects model with center as a random effect and treatment arm as a fixed effect for both analyses. In addition, we will analyze the three repeated measurements (6 weeks, 3 months and 12 months) of USER-Participation-R scores using a single linear mixed effects model with nested random effects for patients within centers and treatment arm as a fixed effect.

For the continuous secondary outcome parameters (CLCE-24, HADS, PROMIS-10 and GSES) we will use the same statistical modelling approach as described above.

The continuous secondary outcome parameter SASC-19 will be analyzed using an unpaired t-test.

With regard to the ordinal scores on the mRS we will calculate the within-group median change scores as the 50th percentile of all individual differences (change from baseline to 1-year outcome assessment). Point estimate and 95% CI of the median difference in change scores between treatment groups will be calculated using the Hedges-Lehmann method [36]. Between-group difference in change scores will be analyzed using the Mann-Whitney test.

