**Methods / design:**

A multicenter, patient-blinded, cluster randomized controlled trial will be performed. Centers will be randomized (1:1) to the intervention group or the usual care group. Patients (> 18 years old) with a neurological confirmed diagnosis of ischemic stroke who can be discharged home without follow-up treatment at an outpatient rehabilitation clinic will be included. In the intervention group, patients will receive a short, individualized, semi-structured consultation by specialized nurses in addition to usual care. This consultation includes 1) screening for cognitive and emotional problems, 2) screening for restrictions in participation, 3) promotion of self-management strategies and 4) a decision tool for referral to rehabilitation services. The intervention will be performed approximately 6 weeks after the stroke at the neurology outpatient clinics and will take approximately 60 min. The control group will receive care as usual. Both groups will be followed-up at 6 weeks, 3 months and 12 months after stroke. The primary outcome will be the level of participation measured with the Restriction subscale of the Utrecht Scale for Evaluation of Rehabilitation on the level of Participation (USER-Participation-R) at 12 months. A cost-effectiveness analysis and process evaluation will be performed alongside.

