### Trial center eligibility and allocation

University and non-university hospitals in the Netherlands will be invited to participate in this study. All centers that intend to participate will be examined for their current stroke care by an online questionnaire and by interviews. Centers will be excluded from the study if one of the following criteria is met:
the current stroke care includes a screening for cognitive and emotional problems using validated screening instruments in the majority of stroke patients, within 3 months after stroke;the current stroke care includes long term follow-up (6 months or longer) with repeated cognitive and emotional assessments, with or without the use of validated screening instruments, in the majority of stroke patients.

After selection, the eligible centers will be randomized by an independent statistician in blocks of two in a 1:1 ratio to the intervention group or the usual care group using the web-based system Randomizer [20].

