### Sample size

Since no USER-Participation-R data are available concerning the participation levels of our target group, we based our sample size calculation on Cohen’s effect size as benchmark for assessing the relative magnitude of differences in participation level between the treatment arms. Although a Cohen’s effect size of 0.35 can be defined as between small and medium, such a difference in mean participation scores may be clinically important. Therefore, it was considered necessary to detect this difference in participation level between both treatment arms. A sample size of six clusters per treatment group (12 clusters in total) with 36 individuals per cluster (216 patients per treatment group; 432 patients in total) achieves 81% power to detect an effect size of 0.35 when the intracluster correlation is 0.01 using a two-sided t-test based on the number of clusters, with a significance level of 0.05 [21]. Anticipating on a 15% attrition rate in each center, we will include (36 / 0.85 =) 43 patients per center, resulting in 258 patients per treatment group and 516 patients in total.

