#### Process evaluation

Quantitative data (reach and dose of the intervention, timing of the intervention, completion of the questionnaires, information provision, duration of the intervention, BFAI and SASC-19) will be analyzed using descriptive statistics. Qualitative data from the focus group interview will be transcribed verbatim. The free text will be coded and categorized for thematic analysis and will be used to analyze the experiences of the nurses from the intervention [39]. Codes will be identified, indexed and transcending themes will be identified using MAX Qualitative Data Analysis (QDA) version 2007.

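### SASC-19 and mRS change are tested as if patients were independent although centres are randomized; at the trial's own ICC of 0.01 the nominal 5% tests would run at about 9%

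*Protocol article*

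**What the plan says.** The unit of randomization is the hospital. The abstract states that "Centers will be randomized (1:1) to the intervention group or the usual care group", and the section on trial center eligibility and allocation adds that "the eligible centers will be randomized by an independent statistician in blocks of two in a 1:1 ratio".

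The Sample size section plans for this: "A sample size of six clusters per treatment group (12 clusters in total) with 36 individuals per cluster (216 patients per treatment group; 432 patients". It obtains its power "when the intracluster correlation is 0.01 using a two-sided t-test based on the number of clusters".

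Under Statistical analysis, Clinical effectiveness, the primary outcome is analysed with a linear mixed model that has centre as a random effect. The same approach is extended to CLCE-24, HADS, PROMIS-10 and GSES. Two outcomes are then treated differently:

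- **SASC-19:** "The continuous secondary outcome parameter SASC-19 will be analyzed using an unpaired t-test".
- **mRS:** "Between-group difference in change scores will be analyzed using the Mann-Whitney test". The median difference in change gets a 95% interval by the Hodges-Lehmann method (printed there as Hedges-Lehmann).

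The same section sets two-sided significance at 0.05 and 95% confidence intervals for the analyses generally, without multiplicity correction. Under Statistical analysis, Process evaluation, SASC-19 appears again in a list of measures ending "BFAI and SASC-19) will be analyzed using descriptive statistics".

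**The concern.** An unpaired t-test, a Mann-Whitney test and a Hodges-Lehmann interval all take patients as independent observations. In this trial, patients of one hospital share an allocation and may share influences on outcome. Any variation between hospitals then enters the treatment comparison, and these methods do not count it. They also use a reference distribution suited to about 430 patients, when the between-arm contrast rests on 12 hospitals, that is 2 × (6 − 1) = 10 degrees of freedom.

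This is not a detail left to a later analysis plan. The article names the tests, in the same section that uses a random centre effect elsewhere.

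For satisfaction, variation between centres is plausible. The Discussion says most hospitals have a single professional doing outpatient stroke care, and the Control group section expects usual care to differ between hospitals. For mRS the argument is weaker. The scale is completed by an unblinded researcher or nurse, so rater differences between centres could contribute, but the outcome is a change score, whose clustering may differ from that of a level.

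At stake is a satisfaction or disability result that is declared significant, or given too narrow an interval, because of differences between hospitals.

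**Working it through.** **Inputs from the protocol article.** Sample size section: k = 6 centres per arm, m = 36 evaluable patients per centre (43 recruited), effect size 0.35, ICC 0.01, two-sided alpha 0.05. The ICC was set for the primary outcome.

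**Step 1: reproduce the plan's own figure.**

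- Design effect: DE = 1 + (m − 1) × ICC = 1 + 35 × 0.01 = 1.35.
- Effective size per arm: 216 / 1.35 = 160.
- Noncentrality: 0.35 × √(160 / 2) = 3.13.
- Power from the noncentral t with 10 df: 80.5%, against 81% stated.

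The same calculation with 430 df gives 87.8%, and ignoring clustering gives 95.3%. Only the version based on the number of clusters matches, so the sample size rests on the principle that the two tests drop.

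**Step 2: what a patient-level test does.** Its standard error is too small by a factor 1/√DE. Under no treatment effect, its actual two-sided error is

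type I error = 2 × [1 − Φ(1.96 / √DE)].

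At ICC 0.01: √1.35 = 1.162; 1 − 1/1.162 = 0.14, so the standard error is 14% too small; 1.96 / 1.162 = 1.687; the error rate is 9.2% and the nominal 95% interval covers 90.8%.

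**Step 3: range.** Every ICC below except 0.01 is an assumption, and 0.01 itself is borrowed from the primary outcome.

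| ICC (m = 36) | DE | SE too small by | Type I error | Width of correct interval (10 df) relative to naive |
|---|---|---|---|---|
| 0 | 1.000 | 0% | 5.0% | not applicable (no clustering) |
| 0.005 | 1.175 | 8% | 7.1% | 1.23 |
| 0.01 | 1.350 | 14% | 9.2% | 1.32 |
| 0.02 | 1.700 | 23% | 13.3% | 1.48 |
| 0.05 | 2.750 | 40% | 23.7% | 1.89 |

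The last column is √DE × 2.228 / 1.96, where 2.228 is the 97.5% point of t with 10 df. With all 43 recruited patients per centre analysed (for example after imputation), ICC 0.01 gives DE = 1 + 42 × 0.01 = 1.42 and a type I error of 10.0%.

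**Step 4: simulation.** The formula in step 2 is for a mean, so it was checked for both tests: 12 centres of 36 patients, no treatment effect, 6,000 runs per ICC, and a five-category ordinal score for the Mann-Whitney test.

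| ICC | Unpaired t-test | Mann-Whitney | t-test on centre means (10 df) |
|---|---|---|---|
| 0.01 | 9.0% | 8.7% | 5.0% |
| 0.02 | 12.7% | 12.0% | 4.8% |
| 0.05 | 24.0% | 22.0% | 5.0% |

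The rank test is inflated slightly less than the t-test. An analysis at centre level holds the nominal 5%.

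**The case against.** The strongest reply is that little rests on these tests. They concern two secondary outcomes in a plan that openly forgoes multiplicity control. The primary outcome, its sensitivity and repeated-measures analyses, and four other secondary outcomes all have a centre effect. This stands, and it limits the weight of the point.

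A second reply is that the amount of inflation is unknown. It stands too. A reader might take 9% as the actual error rate of these tests. The protocol does not support that, because it gives no ICC for SASC-19 or mRS, and with no clustering the tests would be valid. The figure could also be higher than 9%, particularly for satisfaction.

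A reader might also infer that the protocol contradicts itself by testing SASC-19 in one section and describing it in another. The text does not go that far. The process evaluation section does not say that SASC-19 is described only. The Outcomes section says the reporting is sorted by objective, and satisfaction serves two: it is a secondary effectiveness outcome and a process measure of participant responsiveness. A test under one heading and a descriptive summary under the other are compatible.

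None of this defends the choice of tests. No section adds a centre term, a centre-level summary or a cluster-robust variance for either outcome.

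**Conclusion.** The point holds for SASC-19 and for mRS change, and only for these. The named analyses do not match the randomization or the plan's own handling of the other outcomes. If the ICC of 0.01 carried over, with 36 patients per centre, the type I error would be about 9% (9.2% for the t-test by formula, 8.7% for the Mann-Whitney test by simulation) and the standard error 14% too small. Over an assumed ICC of 0.005 to 0.05 the error is about 7% to 24%; at zero it is 5%. These figures assume equal centre sizes.

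The sample size and the primary analysis are not affected, so a reader should not infer that the main conclusion is at risk. This should be fixed before analysis; it is not a fatal flaw.

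**What to change.** **SASC-19.** Replace the unpaired t-test with the linear mixed model already planned for the other outcomes (random centre, fixed arm), applied to the T2 score, with small-sample degrees of freedom based on 12 clusters (about 10).

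**mRS change.** Replace the Mann-Whitney test and its interval with an analysis that respects the centres and has a small-sample reference. A centre-level or centre-permutation analysis with a matching interval keeps the planned change-score measure. A mixed ordinal model is an alternative, but it changes the effect measure to an odds ratio, must state whether it models change or the 12-month score, and needs a small-sample correction. In a simulated linear analogue, a random centre effect fitted by maximum likelihood with a normal reference still gave a type I error of about 7% at ICC 0.01 and 10% at 0.05.

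**Optional wording.** The process evaluation section could say that its descriptive SASC-19 summary is in addition to the between-arm test.

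**Cost.** A few sentences of analysis text and no new data. The loss of precision is real: intervals become about 1.3 times as wide at ICC 0.01 with 10 df, and about 1.9 times at 0.05.

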#### Cost-effectiveness

A trial-based economic evaluation will be conducted according to the Dutch guidelines and will involve a combination of a cost-effectiveness analysis (CEA) and a cost-utility analysis (CUA) [37]. In the CEA effects will be presented as clinical outcomes (i.e. USER-Participation-R). In the CUA, costs are calculated in a similar way as in the CEA, but effects are expressed in quality-adjusted life years (QALYs). Utilities will be derived from the EQ-5D-5L. To estimate the incremental cost-effectiveness, the incremental cost-effectiveness ratio (ICER) will be calculated for both the CEA and CUA. Sensitivity and uncertainty analyses will be performed. We will perform a Budget Impact Analysis (BIA) additionally to the economic evaluation according to the Mauskopf guidelines [38]. The purpose of this BIA is to estimate the financial consequences of adoption and diffusion of the intervention on a national scale.

#### Process evaluation

Quantitative data (reach and dose of the intervention, timing of the intervention, completion of the questionnaires, information provision, duration of the intervention, BFAI and SASC-19) will be analyzed using descriptive statistics. Qualitative data from the focus group interview will be transcribed verbatim. The free text will be coded and categorized for thematic analysis and will be used to analyze the experiences of the nurses from the intervention [39]. Codes will be identified, indexed and transcending themes will be identified using MAX Qualitative Data Analysis (QDA) version 2007.

## Discussion

The current protocol describes a multicenter, patient-blinded, cluster randomized controlled trial. This trial will analyze the clinical effectiveness, cost-effectiveness and implementation of structured screening and patient-tailored care for cognitive and emotional problems compared to care as usual in patients discharged home after ischemic stroke.

While previous studies have examined the effect of screening for cognitive and emotional problems in randomized trials, the majority of these studies did not examine the effect of screening for cognitive or emotional problems on its own, but as part of a larger intervention. Besides, most studies did not use validated screening instruments [36, 40–43]. To the best of our knowledge, only one earlier randomized trial examined the effect of a cognitive assessment, but did so with a rather extensive neuropsychological examination and did not plan follow-up care [44]. Nonetheless, the topics of cognitive outcome and the social aspects of living with stroke have been recognized by patients and health-care professionals as research priorities [45]. Moreover, since cognitive and emotional sequelae are highly prevalent after stroke, national guidelines already recommend an active screening for both sequelae [2, 17, 18]. Therefore, this study aims to fill an important knowledge gap.

The strengths of the study are the following. First, this study will examine the intervention in a large sample of patients in a randomized manner, which will minimize the chances of bias. Second, the local health care professionals will execute the study intervention, therewith reflecting actual clinical practice and increasing external validity as well as facilitating implementation after the trial. Although this might result in variation in conducting the intervention, thereby introducing bias, we consider this as strength since this reflects the future practice, resulting in stronger generalizability of the findings. Third, the intervention was developed by the collaboration of a multidisciplinary team and aims to further improve the collaboration between health care professionals at the neurology department and the rehabilitation department. Fourth, this study examines an important topic as prioritized by previous patient evaluations and evaluates its effectiveness based on Patient Reported Outcome Measures (PROMs) [45, 46]. Fifth, the intervention will be analyzed from both a clinical and economic perspective, and the implementation of the intervention will also be examined.

The following limitations apply to this study. First, since the intervention is a consultation, blinding of the health care professionals is not possible. However, the patient will not be informed whether or not the intervention was supplied; since most outcomes are patient-reported measurements, we expect to minimize the influence of health care professionals being aware of the allocation. Second, a cluster randomization is methodologically weaker than a patient-level randomization. However, a patient-level randomization was considered unfeasible since most hospitals have only one health care professional occupied with stroke care at the outpatient clinics. Besides, if a hospital would have two or more health care professionals providing the stroke care, contamination from the intervention-trained nurse to the untrained nurse would be likely.

In conclusion, this trial will investigate the clinical effectiveness, cost-effectiveness and implementation of active screening and patient-tailored care for cognitive and emotional problems compared to care as usual in patients discharged home after ischemic stroke.

## Data Availability

individual participant data that underlie the results reported in published articles will be shared, after de-identification, with investigators whose proposed use of the data has been approved by a review committee and who signed the data access agreement. Proposals may be submitted beginning 9 months and ending 36 months after the first article publication.

## Abbreviations

BFAI: Barriers and facilitators assessment instrument
BI: Barthel index
BIA: Budget impact analysis
CEA: Cost-effectiveness analysis
CI: Confidence interval
CLCE-24: Checklist for cognitive and emotional consequences following stroke
CT: Computed tomography
CUA: Cost-utility analysis
eCRF: Electronic case report form
EQ-5D-5L: Five-dimensional euroqol
GSES: General Self-efficacy scale
HADS: Hospital anxiety and depression scale
ICER: Incremental cost-effectiveness ratio
MCQ: Medical consumption questionnaire
MEC-U: Medical research ethics committees united
MoCA: Montreal cognitive assessment
MRI: Magnetic resonance imaging
mRS: Modified rankin scale
NIHSS: National institute of health stroke score
NTR: Netherlands trial register
PCQ: Productivity cost questionnaire
PROM: Patient reported outcome measures
PROMIS: Patient reported outcome measurement information system
QALY: Quality-adjusted life years
QDA: Qualitative data analysis
QoL: Quality of life
SASC-19: Satisfaction with stroke-care
TIA: Transient ischemic attack
USER-Participation-R: Restriction subscale of the Utrecht Scale for evaluation of rehabilitation on the level of participation
